## Abstract

**Background:**

Meaningful activity engagement is a critical element of ageing well. Interventions designed to increase activity engagement tend to be activity-specific and do not always meet the needs of older adults with diverse interests and capacities. Behavioural activation (BA) provides a promising person-centred framework for promoting engagement in valued activities. This study will examine the effectiveness of a behavioural activation-based intervention for promoting engagement with life and wellbeing among older adults.

**Method:**

Participants will be randomly allocated to one of two conditions (BA intervention, Active Control) and take part in a six-week intervention that consists of one-on-one weekly sessions of up to one hour to be administered either via telephone or online video conferencing with a trained facilitator. This study will recruit 120 + participants aged 65 + who score at or below the median on a test of life engagement. Participants will complete questionnaires of primary and secondary measures both pre-program, one-week and three months post-program. Participants will also complete a daily diary questionnaire during the fourth and fifth weeks of the intervention. The primary outcome measure is the Life Engagement Test, and secondary outcome measures include assessments of subjective wellbeing, psychological wellbeing, mental health, self-reported health, social engagement, loneliness and life satisfaction.

**Discussion:**

The outcomes from this study will provide evidence as to whether a BA based approach represents an effective method for promoting engagement with life and wellbeing among older community-dwelling adults.

***Trial registration*:**

Australian New Zealand Clinical Trials Registry (Reg no. ACTRN 12621001192875). Trial retrospectively registered 6th September, 2021.

## Background

One factor that frequently features in definitions of what it means to age well is maintaining active engagement with life [1, 2]. Engagement with life refers to participating in multiple forms of valued activity, including social and solitary activity, productive engagement (e.g., paid work or volunteering), and/or contributing to the wellbeing of others and the community [1]. Ongoing engagement is believed to have a positive effect on physical health [3], cognitive function[4, 5] and psychological wellbeing [6]. Older adults themselves have also regularly identified active engagement with life as central to ageing well [7, 8].

Despite the accepted importance of remaining engaged for ageing well, changes and transitions that commonly occur in older adulthood can sometimes hinder engagement in meaningful activity. For example, losses in physical health and functional capacities can have a direct or indirect impact on activity engagement (e.g., through negative effect on access, or changes to caring responsibilities [9, 10]). Other common transitions that occur in older adulthood such as retirement, bereavement, or downsizing may affect activity engagement through their impact on social networks or finances [11, 12]. Additionally changes to society, such as lockdowns triggered by the COVID19 pandemic, can disproportionately impact older adults, who may be subject to stricter lockdown requirements, less likely to qualify for essential work exemptions, and may be less familiar with online alternatives to staying connected with friends and family [13]. The extent to which ageing presents challenges for ongoing engagement with life is reflected in research on social isolation (i.e., a lack of engagement with social networks). For example, social isolation was reported to increase from 5.4% among 18–39 year-olds to 21.7% in 70–79 year-olds in a recent population-based study of older Germans [14]. A recent US study showed similar rates of isolation among adults aged 65 and older, with almost one-in-four (24%) characterised as socially isolated [15].

Despite age-related challenges, ongoing activity engagement represents an element of ageing well that may be highly amenable to intervention. Multiple programs have been trialled, but these tend to be activity specific (e.g., [16–18]) and as such are not universally appropriate for people with different preferences or abilities. Furthermore, activity-specific programs that follow a “one-size-fits-all” approach may be less likely to fulfill psychological needs of competence, relatedness and autonomy that are important for autonomous motivation, whereby activity is volitional and has intrinsic value [19].

### Behavioural activation as a person-centred meaningful activity intervention

To address this need for a person-centred activity engagement intervention among older adults we have designed an intervention based on the principles of behavioural activation (BA). BA therapy was originally designed to treat depression, and can be used successfully alone, or in conjunction with other cognitive behavioural strategies [20, 21]. The BA model assumes that depression is maintained through a decrease in reinforcing activity and an increase in avoidance behaviours that often occurs with depressive symptoms. Low positive reinforcement increases the symptoms of depression, which can cause the person to withdraw from reinforcing behaviour even further, creating a negative feedback loop. BA assists clients to interrupt that negative cycle by proactively scheduling pleasurable and meaningful activities to support a lifestyle that is more reinforcing, which can reduce symptoms of depression and increase capacity for more reinforcing activity. BA includes activity monitoring to help participants identify patterns in their behaviours, to observe where and how their schedules could incorporate more pleasure or meaning, and to note the connections between activity engagement and mood. BA also includes personal values exploration to identify activities that will be the most reinforcing to an individual and incorporates problem solving to overcome barriers to activity engagement such low motivation, poor energy and concentration levels [22]. Importantly, given the focus of the present study, BA has also been found to be effective among community samples where the focus of treatment is shifted from treating depression to promoting wellbeing [20, 23]. Among older adults, BA has been successfully used to improve quality of life, functional disability and cognitive performance [24, 25]. Whether BA-based approaches provide a direct means of enhancing engagement with life more generally among older community-dwelling adults has not yet been examined.

We propose that the BA approach can have utility not just in reducing depressive symptoms, but also in supporting older adults’ engagement with life (and in turn wellbeing) by facilitating processes of effective self-regulation. A central means through which older adults adapt to changing life circumstances is through regulating their goals in ways that provide an optimal fit with their available resources [26, 27]. For example, successful development depends on making sound judgements about when to invest resources such as time, energy and money into goals that are valued and achievable (assimilation), and when to abandon and de-value goals that are no longer attainable (accommodation, [28]). Importantly, when goals are abandoned, successful development often depends on the ability to reengage with new goals [29]. For example, a person might mobilise their resources to support their efforts as part of an outdoor environmental volunteering group, but when physical limitations make the work no longer possible or enjoyable, this goal might be abandoned in favour of contributing to this (or another) cause by taking on an administration-focused role that requires less physical exertion.

The BA approach focuses on working with participants to identify their values, and activities that are consistent with those values (e.g., [20]). Participants are encouraged to reflect on the degree to which their current activities align with their values, and to identify and schedule activities that are important to them. The BA approach also involves identifying challenges to activities (i.e., blocked goals) and encourages participants to use effective strategies around selecting alternative values-consistent activities and identifying the supports (e.g., social support) needed to make them attainable. By supporting processes of self-regulation (assimilation, accommodation, goal re-engagement) in relation to activities that are values-consistent, we expect participation in a BA program to result in improvements in engagement with life among older adults.

### Study aims

The proposed randomised controlled trial has several objectives, specifically:

To determine the impact of a 6-week BA intervention compared to an active control wellbeing intervention on meaningful activity engagement among older adults from the general population at both one week and three months post-intervention.Determine the impact of BA compared to active control on secondary measures of wellbeing, psychosocial functioning and health, including subjective wellbeing (positive and negative affect and life satisfaction), psychological well-being (flourishing, self-compassion) social engagement and loneliness, mental health (symptoms of depression and anxiety), aspects of self-regulation (goal disengagement and goal re-engagement) and self-reported health.Gain further feedback about program acceptability through a participant survey at the completion of the program.

It is hypothesised that the BA intervention will have a greater positive impact on meaningful activity engagement compared to the active control condition at one week follow-up. This was based on the brief positive psychology interventions in the active control condition being selected on the basis that they aim to increase wellbeing, but do not directly target engagement with activities to enhancing wellbeing.

Participants will also complete a 14-day daily questionnaire (see methods) focusing on daily exposure to stressful events, self-compassion and affect.

Finally, researchers have emphasised the value in conducting intensive longitudinal research as part of clinical trials as a means of providing more ecologically valid data that can be used to examine within-person processes (e.g., [30]). Building on emerging research concerned with short-term variability in self-compassion (e.g., [31]) the study will also include a 14-day daily diary embedded within the larger project. As an observational sub-component of the larger trial, the daily diary data component will allow examination of short-term daily linkages between stressor exposure and affect, and whether affective reactivity to stressors is lower on days when participants report higher self-compassion. Although it will be necessary to control for treatment condition in these analyses, we do not have a priori expectations regarding possible treatment effects. These analyses will be exploratory and do not relate directly to evaluation of the intervention; details of the daily diary component are reported below for completeness.

## Methods/design

### Design

The ELMS is a randomised control trial, that investigates whether an intervention based on BA principles improves life engagement and wellbeing compared to an active control condition, specifically a multi-component positive psychology intervention (MCPPI). Participants will be randomly allocated to one of the two conditions (BA, MCPPI) and will take part in an intervention consisting of six weekly one-on-one sessions of up to one hour, to be administered by trained facilitators via telephone or web conferencing (based on participants’ preference). Program efficacy will be determined by assessment at three time points: baseline (pre-intervention), 1 week and 3 months post intervention. All participants will also complete a daily questionnaire for two weeks between sessions 4 and 6. A summary of the study periods and assessments are provided in Table 1.

**Table 1 Tab1:** Summary of study phases and assessment measures

Time point	Pre-program	Baseline	Program (6 weeks)	1-week post-program	3-month post-program
Enrolment					
Eligibility screen (Life Engagement Test)^a^	X				
Informed consent	X				
Allocation to condition	X				
Intervention					
Treatment: BA			↔		
Active control: MCPPI			↔		
MOCA-blind			X (wk 5)		
Daily questionnaire (2 weeks)			X (wk 4–6)		
Assessment					
Demographics		X			
Alcohol and tobacco use		X			
Pain and physical health		X		X	X
SPANE		X		X	X
Self-compassion scale		X		X	X
BADS		X		X	X
HADS		X		X	X
Life engagement test		X		X	X
UCLA loneliness scale		X		X	X
Flourishing scale		X		X	X
Satisfaction with life scale		X		X	X
Engaged living scale		X		X	X
Social networks scale		X		X	X
Goal adjustment scale		X		X	X
Client satisfaction questionnaire				X	
Daily questionnaire assessment					
State self-compassion			X		
Daily affect scale			X		
DISE			X		
Eudaimonic wellbeing			X		

*BA* Behavioural activation;* BADS*  Behavioural Activation for Depression Sale;* DISE*  Daily Inventory of Stressful Events;* HADS* Hospital Anxiety and Depression Scale;* LET* Life Engagement Test;* MCPPI* Multi component positive psychology intervention;* SPANE* Scale of Positive and Negative Experience

^a^Participants are eligible if they score at or below the mean LET reported in previous studies (see *Participants*)

### Participants

Older adults aged 65 + from the general population, who have a purpose in life (Life Engagement Test) score at or below the population mean in previous community samples [32] will be eligible to participate. Those with substantial hearing loss, difficulty with English or advanced cognitive impairment (or any other difficulties that meant they could not feasibly take part in a telephone-based intervention, as determined by either the recruiter, or the facilitator at first contact) would not be eligible to participate. Potential participants will be initially identified utilising a list of older adults who have agreed to be contacted for future research participation, maintained by the Adult Development Lab at Flinders University, Adelaide, South Australia as well as through advertisements in Weekend Plus, a digital magazine for older adults produced by the South Australian Government, and email invitations sent to online networks such as the South Australian Office for Ageing Well Feedback Network (a group of older adults who have indicated a willingness to be contacted about research projects or government initiatives). Participants will either be contacted by telephone (e.g., those on our database) or will complete an online screening survey to determine eligibility. To date, all participants recruited have resided within South Australia in either metropolitan, regional and rural areas. Future participants may also be recruited through industry partner organisations such as ECH Inc.

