### Study timeline

Older adults who are on a pre-existing list maintained by the Adult Development Lab will be initially contacted by telephone by a research assistant. They will be provided with details of the study, and if they indicate they are interested in participating, they will be administered the LET over the phone to assess their eligibility to participate. Participants who are recruited by online advertisements will be invited to follow a link where they will be provided some information about the study and invited to complete the LET online to determine eligibility. Participants undertaking the full 6-item LET at telephone screening will be eligible to participate if they score at or below 25. Participants undertaking the online screening will be administered a 5-item version of the LET and will be eligible if they score at or below 21 (the mean of the 5-item scale in a community sample of older adults assessed as part of the broader project, N = 431). The final LET item “I have lots of reasons for living” will be excluded for online participants to reduce the possibility of negative feelings among some participants, given that the item would not appear within the context of either a larger survey, or with the presence of the telephone interviewer as an immediate source of support and/or information. The decision to exclude the final item from the online screener was also based on previous data indicating strong item-specific ceiling effects (M = 4.43 (SD = 0.86) on a scale of 1 to 5; [32]) suggesting limited discriminatory value. All eligible participants will be sent, by post or email, the study information sheet, consent form and baseline questionnaire (marked with a unique 3-digit identifier) to complete and return. Those who elect to receive the baseline by email will be sent a link to the baseline questionnaire hosted on the Qualtrics Online Survey Platform. Once the baseline questionnaire is completed participants are considered fully recruited into the study. Using simple randomisation via Microsoft Excel, participants are then allocated to treatment condition. Randomly allocated to treatment condition, sent the corresponding intervention manual and allocated to a study facilitator. The facilitator will contact the participant by telephone to set up a time for the first session and will be responsible for all contact from that participant from then on.

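### The facilitator may rule a person ineligible at first contact, which falls after randomisation and very probably with the arm known, so the plan permits post-randomisation exclusions that could bias the primary comparison

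*Protocol article*

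**What the plan says.** **Who decides eligibility.** The Participants section lists hearing, English and cognition as grounds for exclusion, then adds in brackets "any other difficulties that meant they could not feasibly take part in a telephone-based intervention". The decision is made "as determined by either the recruiter, or the facilitator at first contact) would not be eligible to participate". No threshold is given.

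**Order of events.** Study timeline describes the LET screen (by telephone or online), then consent and the baseline questionnaire. It continues: "Once the baseline questionnaire is completed participants are considered fully recruited into the study". Next, "Using simple randomisation via Microsoft Excel, participants are then allocated to treatment condition". The participant is then "sent the corresponding intervention manual and allocated to a study facilitator". Only after this, "The facilitator will contact the participant by telephone to set up a time for the first session".

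**Blinding.** The Active control section describes participants as blinded to which condition is the intervention. No such statement is made about facilitators, who are trained to run the sessions of both arms.

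**Follow-up and analysis.** Study timeline has the two follow-up questionnaires posted or emailed when participants have finished the intervention. Sample size and analysis specifies a linear mixed model on all available data, with missing values handled under FIML. The article does not say what happens to a randomised person whom the facilitator then finds ineligible.

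**The concern.** An eligibility decision protects a trial only if it is made before allocation, or by someone who does not know the allocation. Here one of the two named decision-makers does not meet the participant until after allocation. That person has been assigned to deliver a particular arm, whose manual has already been sent. The criterion is open-ended, and the only formal cognitive measure described, the MOCA-Blind, comes at week 5, so an earlier exclusion on feasibility would rest on judgement.

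If facilitators exclude different numbers or different kinds of people in the two arms, those who remain are no longer the groups that randomisation formed. The mixed model adjusts for baseline LET. It does not adjust for the characteristics that would lead someone to be judged unable to take part.

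A second consequence is harder to repair. Because the questionnaires are tied to completing the intervention, a person ruled out at the first call may never be sent one. An analysis plan can define who is analysed, but it cannot recover outcomes that were not collected.

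**Working it through.** **1. Sequence.** Setting the two sections side by side:

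| Step (Study timeline) | Facilitator involved? |
|---|---|
| LET screen by telephone or online | No |
| Consent and baseline; person counts as recruited | No |
| Simple randomisation | No |
| Arm's manual sent, facilitator assigned | Assigned here |
| Facilitator telephones to arrange session 1 | First contact |

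The facilitator's first contact, at which the Participants section allows a ruling of ineligibility, cannot come before randomisation. Table 1 marks "Allocation to condition" under the pre-program column, to the left of baseline, whereas Study timeline puts it after baseline. On either placing it precedes the facilitator's call, so this is only a labelling matter.

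**2. The plan's own figure.** Sample size and analysis gives d = 0.52, alpha 0.05, power 0.8 and 60 per group. A two-sided two-sample t-test needs 59.03, rounded up to 60, and power at 60 per group is 0.806. The figure reproduces. With a difference of about 2 LET units, the implied SD is 2 / 0.52 = 3.85.

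**3. Possible size of the bias.** The documents give no exclusion rate and no outcome difference, so both are assumptions. Suppose a fraction f of one arm is excluded, and those people would have scored g SD below that arm's full mean at follow-up. The mean of those retained rises by

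shift = g × f / (1 − f).

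| Excluded of 60, one arm only | f / (1 − f) | Shift, g = 0.5 to 1.0 (SD) | LET units (× 3.85) | Share of 0.52 | Two-sided type I error |
|---|---|---|---|---|---|
| 1 | 1/59 = 0.017 | 0.008 to 0.017 | 0.03 to 0.07 | 1.6 to 3.3% | 0.050 to 0.051 |
| 3 | 3/57 = 0.053 | 0.026 to 0.053 | 0.10 to 0.20 | 5.1 to 10.1% | 0.052 to 0.060 |
| 6 | 6/54 = 0.111 | 0.056 to 0.111 | 0.21 to 0.43 | 10.7 to 21.4% | 0.061 to 0.093 |

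The type I error uses a standard error of √(2/60) = 0.183 SD. All values are before baseline adjustment, which would remove part of the shift.

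**4. Equal rates.** With exclusions in both arms, the bias is the difference between the two arms' shifts. If 3 of 60 are excluded in each arm but g is 1.0 in one and 0.5 in the other, the bias is 0.053 − 0.026, or about 0.03 SD. Equal rates remove the bias only if the people excluded are also alike.

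**The case against.** The order of events is not in dispute. The case on the other side concerns scope, likelihood and size, and much of it stands.

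- **Scope.** The clause naming the facilitator sits inside the bracket about other difficulties. It may not extend to hearing, English or cognition, and the text does not settle this. The open-ended part alone is enough for the point.
- **Only check for online recruits.** A reader might infer that the facilitator's call is the sole check of these criteria for people recruited online, since no conversation before allocation is described. The documents do not support that. The Participants section mentions an online survey to determine eligibility, and Study timeline details only its LET part. A condensed article's silence about other questions proves nothing, and written forms already filter somewhat on English and cognition.
- **Mechanism.** The criterion is feasibility of a telephone programme, which is common to both arms. Between-session work is stressed more in BA, but the article does not name it as a ground for exclusion, and BA tasks left undone are completed with the facilitator at the next session. Differential exclusion is possible; nothing shows it to be likely.
- **Analysis set.** If those excluded stay in the model with their baseline data, they become early dropouts and FIML recovers whatever baseline LET predicts. An analysis plan not shown here may say so. It would still lack their outcomes if no questionnaire was sent.
- **Sample size.** A reader might infer that exclusions take the analysed number below 60 per arm. That does not follow: the Abstract's target is 120 or more, and simple randomisation does not fix the arms at 60.

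**Conclusion.** The concern holds as a matter of sequence. The plan permits eligibility exclusions after randomisation, on an open-ended judgement, by the person who will deliver the arm. That this person knows the arm is an inference, though a strong one, since no facilitator blinding is described. The follow-up arrangement means that those excluded may provide no outcome data.

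The size of any bias cannot be determined from the documents. Under the stated assumptions, with exclusions in one arm only, it is negligible for one exclusion, about 0.03 to 0.05 SD for three of 60, and up to 0.11 SD for six of 60, in each case before baseline adjustment. A reader might conclude that the primary result is bound to be distorted. The documents do not support this, because they show neither that such exclusions are common nor that they differ by arm. This should be fixed because the remedy is cheap and missed outcomes cannot be collected later, but it is not a fatal flaw.

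**What to change.** 1. In Participants, delete the clause that gives the facilitator an eligibility decision, and complete every eligibility check before randomisation. The recruiter does this by telephone. For online recruits, add screener questions on hearing, English and telephone feasibility if they are not already there, or have the existing research assistant make a short call.
2. State that everyone randomised is sent both follow-up questionnaires and is analysed in the allocated arm, even if sessions prove not feasible.
3. Recruitment had already begun when the article was written. For participants already randomised, report facilitator exclusions by arm and seek their follow-up data where consent allows.
4. In Table 1, move the allocation mark to follow baseline.

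The cost is a wording amendment and a few screener questions or one short call per online recruit.
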